## 1. Background

In laparoscopic surgery, especially when surgery is performed in morbidly obese patients, surgical conditions are determined in a major if not exclusive part by the depth of the neuromuscular block. A deep block (PTC 1-2) is often associated with improved surgical conditions and is therefore requested by the surgeons. However, a deep block comes at the expense of a variety of items that may conflict with its use including long recovery times, postoperative ventilation and impaired postoperative breathing conditions with atelectasis and hypoxia. With the introduction of Sugammadex there is now the possibility to reverse an even deep surgical block. This may overcome most of the issues mentioned.

Previously we showed that a deep NMB coincided with favorable surgical conditions in lean patients undergoing elective laparoscopic retroperitoneal surgery for prostatectomy or nephrectomy (See Figure 1). During a moderate NMB 20% of surgical scorings were less than good, during deep NMB 99% of scorings were excellent or good, 67% were excellent.

[figure not shown]

**Figure 1:** Effect of depth of NMB of scoring of the surgical field using the Leiden Surgical Rating Scale in lean patients undergoing retroperitoneal urologic surgery. The scores range from 1 (extreme poor conditions) to 5 (excellent conditions). Data are from Martini et al. 2014.

In the current study we will examine the effect of the depth of the neuromuscular block on two major end-points:

**(1) Surgical conditions**, with as main research question *“Does a deep surgical block indeed improve surgical conditions in case of laparoscopic surgery in morbidly obese patients for bariatric surgery?”* The surgical condition will be determined from a surgical rating condition scale, the Leiden Surgical rating Scale. This is a 5-point ordinal scale ranging from 1 = poor condition to 5 = optimal surgical conditions. The surgeon will score the condition at 5 min intervals. At the time of scoring also the intraabdominal pressure will be monitored.

**(2) Postoperative pain**, with as main question *“Does a deep block coincide with less pain compared to a moderate block in the recovery period?”*

Secondary end-points include:

(1) The hemodynamics during surgery with the main research question *“Does a deep neuromuscular block coincide with improved hemodynamics during surgery and less postoperative pain?”*

(2) Cardiorespiratory conditions in the post-anesthesia care unit, with the main research question *“What is the effect of reversal with Sugammadex of a deep surgical muscle block on postoperative breathing activity as measured by respiratory rate and saturation”*

(3) Sedation (Using the Ramsey Sedation Scale) in the post-anesthesia care unit, with the main research question *“Does a deep block coincide with less sedation compared to a moderate block in the recovery period?”* and

(4) The Postoperative Quality of Recovery Scale (PQRS), with the main question *“Irrespective of depth of the neuromuscular block during surgery, is the quality of recovery similar in patients that were reversed with sugammadex?”*.

To address these research questions, we will relax morbidly obese patients undergoing bariatric surgery with rocuronium. Patients will be randomly assigned to receive a moderate neuromuscular block with a TOF of 1-2 or a deep NMB (deep block) with a TOF of zero and PTC of 1-2. Rocuronium will be administered as bolus infusion ranging from 0.6 – 1 mg/kg. Titration to effect will be performed immediately after intubation.

After surgery has ended patients that received a moderate NMB will be reversed with 2 mg/kg sugammadex, while patient that received the deep block will receive 4 mg/kg sugammadex. Extubation will be performed when the TOF ratio > 0.9 and the patients breathes adequately.

In the post-anesthesia care unit the cardiorespiratory parameters (blood pressure, heart rate oxygen saturation), the level of pain (on an 11-point numerical rating scale), sedation and the PQRS will be measured at 15 min intervals until discharge to the ward.

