## **2. Objectives and Hypotheses**

### *Main Objectives*

- To assess whether the implementation of a deep neuromuscular block (NMB) (PTC 1-2) combined creates optimal surgical conditions as measured by the surgeon (using the 5-point Leiden surgical rating scale) *versus* a moderate neuromuscular block (TOF 1-2) in morbidly obese patients undergoing bariatric surgery.
- To assess whether reversal of the deep NMB with sugammadex 4 mg/kg results in optimal analgesic conditions in the post-anesthesia care unit.

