## 5. Power and Statistical Analysis

The investigator will be responsible for the data analysis. The analysis will be performed on a blinded data set after medical/scientific review has been completed and all protocol violations have been identified and the data set has been declared complete.

There are two primary end-points: The Leiden Surgical rating Scale (see table above) and postoperative pain. The hypothesis of the study is that a deep neuromuscular block will coincide with improved surgical conditions as compared to a standard of care block and less postoperative pain.

Secondary end-points include: hemodynamics during surgery (blood pressure, heart rate); and sedation/SpO2/blood pressure/heart rate in the recovery period. The hypotheses are: Deep block coincides with optimal hemodynamic conditions during surgery; Deep block coincides with less pain in the recovery room albeit without any cardiorespiratory compromise.

**Sample size: Powering the study on Surgical Rating Scale:** The estimated mean difference between the treatment groups is conservatively estimated to be at 0.5 (but probably > 1), and combined with various assumptions on the variability (that is anticipated to be approximately 0.4), a sample size of 20 per group would provide at least 90% power to observe the expected difference (see table below):

MEAN DIFFERENCE between treatments

|      | SD 0.4    | SD 0.45   | SD 0.5    |
|------|-----------|-----------|-----------|
| 0.4  | 23        | 28        | 34        |
| 0.45 | 18 | 23        | 27        |
| 0.5  | 15        | 19 | 23        |
| 0.55 | 13        | 16        | 19 |
| 0.6  | 11        | 13        | 16        |

Table: Sample size per group by range of mean group differences and standard deviations (SD) at 90% power.

**Powering postoperative pain:** Assuming a difference in pain score between the two treatment groups of 1.0 (numerical ratings scale), a SD of 1.5 (CV 150%), and alpha of 0.05, the study has a power > 0.9 to detect a difference with 100 subjects. We therefore decided to enrol 100 patients (50 per group) in this study allowing the detection of a difference in Surgical rating Scale and pain in the recovery room. This approach ensures adequate power to detect significant and clinically relevant differences in the surgical rating scale and postoperative pain. We expect no difference in PQRS, sedation and respiratory parameters.

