Statistical analysis will be by analysis of variance or t-test as specified by Martini et al. Br J Anaesth 2014. Descriptive and inferential statistics were used for analysis. All data are first tested for normality by a Q-Q plot, a Kolmogorov-Smirnov and a Levene's test.

Descriptive statistics are used to outline characteristics of included patients. Continuous normally distributed variables are expressed by their mean and standard deviation, not normally distributed data by their median and range. To test groups, categorical variables are tested using the Pearson's Chi-square test or Fisher's exact test, when appropriate. Normally distributed continuous data are tested with Students t-test and in case of skewed data, with the Mann-Whitney U test.

**Amendment:** After consultation with a statistician we decided to analyze the Surgical Rating Scale and the pain score as continuous variables, as we are dealing with at least 5 categorical scales (see Martini et al., 2014). Statistical analysis on the Surgical Rating Scale and pain score in the post anesthesia care unit will then be by linear-mixed model with an autoregressive covariance structure. *Post hoc* analysis was by t-test (with  $p < 0.01$  considered significant). Pain scores on the ward (wound pain, deep pain shoulder pain) will be averaged and the group comparison will be by t-test.

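### Two aims credit outcomes to sugammadex reversal, which the randomised arms cannot isolate; similarity and no-compromise aims are paired only with difference tests; sedation has two conflicting hypotheses

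*Protocol*

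**What the plan says.** **Aims that name reversal.** The second main objective in Section 2 is "To assess whether reversal of the deep NMB with sugammadex 4 mg/kg results in optimal analgesic conditions in the post-anesthesia care unit". The second secondary question in Section 1 is "What is the effect of reversal with Sugammadex of a deep surgical muscle block on postoperative breathing activity", measured by respiratory rate and saturation. Sections 1, 3 and 4 all state that both randomised groups are reversed with sugammadex, 2 mg/kg after moderate block and 4 mg/kg after deep block.

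**Aims of similarity or absence of harm.** For the Postoperative Quality of Recovery Scale (PQRS), Section 1 asks "Irrespective of depth of the neuromuscular block during surgery, is the quality of recovery similar in patients that were reversed with sugammadex". Section 5 gives the hypothesis "Deep block coincides with less pain in the recovery room albeit without any cardiorespiratory compromise" and ends its sample-size paragraph with "We expect no difference in PQRS, sedation and respiratory parameters".

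**Sedation.** Section 1 asks "Does a deep block coincide with less sedation compared to a moderate block in the recovery period", whereas the Section 5 sentence just quoted expects none.

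**Analysis.** Section 5 names analysis of variance, the t-test, and chi-square or Fisher's exact test, and states "Normally distributed continuous data are tested with Students t-test and in case of skewed data, with the Mann-Whitney U test". The amendment in Section 5 adds a linear mixed model for the surgical rating and the pain score in the recovery unit only. The protocol states no margin and no rule for reading a confidence interval. Power is given only for detecting a difference in surgical rating and in pain.

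**The concern.** There are three linked problems.

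1. An aim that names the effect of reversal needs a contrast in which reversal varies while block depth does not. The randomised design has no such contrast. A pain difference, which is one of the two primary end-points, could be reported as an analgesic effect of sugammadex when it is equally compatible with an effect of block depth.
2. An aim of similarity or of no compromise needs a criterion for how large a difference is still acceptable. A test for a difference supplies none, and in a trial of this size it often misses moderate differences. Section 1 gives impaired breathing, atelectasis and hypoxia as costs of deep block that sugammadex may overcome, so a reassuring statement on breathing is one that readers would act on.
3. With two hypotheses for sedation, either a lower level or no difference could afterwards be presented as the expected result.

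**Working it through.** **Step 1. What the randomised arms can separate.**

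| Arm | Block depth | Sugammadex |
|---|---|---|
| Group 1 | moderate | 2 mg/kg |
| Group 2 | deep | 4 mg/kg |

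Depth and reversal dose change together, and no randomised arm goes without sugammadex. The arm difference is the effect of depth and reversal dose combined, and no sample size splits it. The third group of 50 in the amendment on comparing the rating scale among surgeons does not help. It is added post hoc, its reversal is not stated, and its purpose is to compare surgeons' ratings.

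**Step 2. Reproduce the plan's own power figure.** Inputs from Section 5: pain difference 1.0, SD 1.5, alpha 0.05 (taken as two-sided), 50 per group.
- Standard error in SD units: sqrt(2/50) = 0.20.
- Standardised difference: 1.0/1.5 = 0.667. Noncentrality: 0.667/0.20 = 3.33.
- Power: Phi(3.33 − 1.96) = 0.915 by normal approximation, 0.910 by the exact t-test.

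The stated power above 0.9 is correct for detecting a difference in pain. It says nothing about showing similarity on other outcomes.

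**Step 3. Precision for the similarity aims.** The protocol gives no SD for PQRS, respiratory rate or SpO2, so the results are in units of the SD of whichever single summary per patient is compared.
- 95% half-width: t(0.975; 98 df) × sqrt(2/50) = 1.984 × 0.20 = 0.397 SD.

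**Step 4. How often a real difference is non-significant.** For a true difference d, the probability is approximately Phi(1.96 − d/0.20). For d = 0.3 this is Phi(0.46) = 0.68. Exact noncentral-t values are:

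| True difference (SD) | Probability of p > 0.05 |
|---|---|
| 0.2 | 83% |
| 0.3 | 68% |
| 0.4 | 49% |
| 0.5 | 30% |

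**Step 5. What an interval rule could deliver.** Suppose the true difference is zero and similarity is claimed only if the 95% interval lies within ±m. With the SD held at its true value, the probability is 2·Phi((m − 0.397)/0.20) − 1. The last column allows for the SD being estimated. The margins are assumptions.

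| Margin m (SD) | SD held fixed | SD estimated |
|---|---|---|
| 0.4 | 1% | 5% |
| 0.5 | 39% | 39% |
| 0.6 | 69% | 69% |

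The two columns differ only at 0.4 SD, where the margin almost equals the half-width and small changes in the estimated SD decide the result.

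**Step 6. Sedation.** The Section 1 question is directional and the Section 5 expectation is null. No text ranks one above the other.

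**The case against.** The strongest reply is that the passages are research questions, an objective, a hypothesis and an expectation, and none is a claim. A reader might infer that the protocol will treat a non-significant p-value as proof of similarity. No sentence says so, and the expectation of no difference closes a sample-size paragraph and is not a decision rule. That stands, and it limits the point to a mismatch between the aims and the tests named.

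A reader might also infer that the pain comparison is invalid. It is not. The pain question in Section 1 and the hypotheses in Sections 2 and 5 compare deep with moderate block, and as a comparison of the two strategies that contrast is randomised and adequately powered. Only the second main objective and the respiratory question name reversal.

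Nor is it a flaw for the PQRS question that both arms receive sugammadex, since that question is confined to patients reversed with it. What that question lacks is a criterion for similar.

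Finally, margins and the reading of secondary end-points are often left to a statistical analysis plan, which is not at hand. Their absence alone would not be a finding. What remains is that the protocol itself words aims as similarity and absence of compromise, and itself fixes a set of tests that cannot answer them.

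**Conclusion.** The point holds in this limited form. The second main objective and the respiratory question ask for an effect that the randomised arms cannot isolate. The trial can compare deep block with its reversal dose against moderate block with its reversal dose, and nothing finer.

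The similarity and no-compromise aims cannot be met by the tests named. At 50 per arm the data remain compatible with differences up to about 0.40 SD either side of the estimate, and a true 0.3 SD difference goes undetected about two times in three. The sedation hypotheses contradict each other.

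These figures assume 50 analysable patients per arm, a two-sided 5% level, and one roughly normal summary per patient. Neither powered superiority comparison is undermined, so the consequence lies in what may be concluded.

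**What to change.** 1. Reword the second main objective and the respiratory question as a comparison of the two strategies, each being a block depth together with its reversal dose.
2. State one hypothesis for sedation and use it in both Section 1 and Section 5.
3. For PQRS, respiratory rate and SpO2, report the arm difference with a 95% confidence interval, and state that a non-significant test will not be taken as similarity or as absence of compromise. Then choose one of two courses. Either call these outcomes descriptive, or fix a margin for each before unblinding, claim similarity only if the interval lies inside it, and otherwise report that similarity was not shown.

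The cost is wording and intervals. No treatment, procedure or sample size changes. The downside of the margin course is that most similarity claims would end as not shown unless the margin is wide, as Step 5 shows. If no margin that wide is clinically defensible, the descriptive course is the sounder choice.

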## **2. Objectives and Hypotheses**

### *Main Objectives*

- To assess whether the implementation of a deep neuromuscular block (NMB) (PTC 1-2) combined creates optimal surgical conditions as measured by the surgeon (using the 5-point Leiden surgical rating scale) *versus* a moderate neuromuscular block (TOF 1-2) in morbidly obese patients undergoing bariatric surgery.
- To assess whether reversal of the deep NMB with sugammadex 4 mg/kg results in optimal analgesic conditions in the post-anesthesia care unit.

### *Hypothesis*

- Deep NMB combined will result in a significant improvement of surgical conditions compared to moderate NMB, combined with less pain postoperatively;

### 3. Study Design

This is a randomized controlled trial (RCT) performed in 100 morbidly obese patients that will undergo elective laparoscopic surgery for bariatric surgery under a moderate neuromuscular block (GROUP 1) or a deep neuromuscular block (GROUP 2). All procedures will be executed in compliance with the current revision of the Declaration of Helsinki and Good Clinical Practice guidelines. The trial starts after the medical ethical committee has approved the study protocol and will have a maximum duration of one year.

*Inclusion criteria:* ASA 1-3, 18 years or older and younger than 66 years; BMI > 34 kg/m^2; ability to give informed consent; elective bariatric surgery.

*Exclusion criteria:* known or suspected neuromuscular disorders impairing neuromuscular function; allergies to muscle relaxants, anesthetics or narcotics; a (family) history of malignant hyperthermia; women who are or may be pregnant or are currently breast feeding; renal insufficiency, as defined by serum creatinine x 2 of normal, or urine output < 0.5 ml/kg/h for at least 6 h. When available, other indices will be taken into account as well such as glomerular filtration rate < 30 ml/h and proteinuria (a ratio of 30 mg albumin to 1 g of creatinine).

Patients in GROUP 1 will receive intravenous rocuronium bolus infusions until the TOF = 1 or 2; patients in GROUP 2 will receive intravenous rocuronium bolus infusions until the TOF = 0 and PTC = 1 or 2. The TOF will be measured by TOF watch at 5 min intervals allowing titration of the neuromuscular block to effect. This procedure is similar to that of Dubois et al. (Eur J Anaesthesiol, 2014). **The surgeon will be blinded to the level of muscle relaxation.** The attending anesthesiologist will be made responsible for both the administration of the muscle relaxant and degree of NMB. The anesthesia consists of propofol plus remifentanyl aimed at keeping the BIS at a value of 50 ± 10.

During surgery the surgeon will score the surgical conditions according to the Leiden Surgical Rating Scale (Martini et al., 2014): The score are defined as follows:

- 1 Extremely poor conditions:** The surgeon is unable to work due to coughing or due to the inability to obtain a visible laparoscopic field because of inadequate muscle relaxation. Additional muscle relaxants must be given.
- 2 Poor conditions:** There is a visible laparoscopic field but the surgeon is severely hampered by inadequate muscle relaxation with continuous muscle contractions and/or movements with the hazard of tissue damage. Additional muscle relaxants must be given.
- 3 Acceptable conditions:** There is a wide visible laparoscopic field but muscle contractions and/or movements occur regularly causing some interference with the surgeon's work. There is the need for additional

muscle relaxants to prevent deterioration.

- 4 Good conditions:** There is a wide laparoscopic working field with sporadic muscle contractions and/or movements. There is no immediate need for additional muscle relaxants unless there is the fear for deterioration.
- 5 Optimal conditions:** There is a wide visible laparoscopic working field without any movement or contractions. There is no need for additional muscle relaxants.

After the surgery has finished patients will be reversed with sugammadex: GROUP 1 will receive 2 mg/kg, GROUP 2 4 mg/kg. This will be known by the attending anesthesiologist only and will be blinded to surgeon and the PACU team.

In the recovery room (post-anesthesia care unit) the following measurements are made at 10 min interval: blood pressure, heart rate, respiratory rate, SpO2, pain, PQRS and sedation levels by the recovery room personnel, who all will be blinded to treatment.

[figure not shown]

#### 4. Study procedures

This is a randomized controlled parallel study on the effect of deep *versus* moderate rocuronium-induced NMB (PTC 1-2 vs. TOF 1-2) in patients with morbid obesity undergoing elective bariatric laparoscopic surgery under propofol/remifentanyl anesthesia.

100 patients (18-65 yrs) that will undergo elective bariatric surgery under general anesthesia will be randomized to a moderate neuromuscular block according to standard of practice with TOF values of 1 or 2 (GROUP 1) or a deep neuromuscular block with TOF values of zero and a post-tetanic count of 1 or 2 (GROUP 2). Anesthesia will be induced with propofol and rocuronium (in GROUP 1: dose = 0.6 mg/kg, in group 2: dose = 1 mg/kg) and maintained with propofol and remifentanyl according to the fast track protocol for bariatric surgery. The TOF and PTC will be measured at 5 min interval; When the TOF and PTC are off target additional rocuronium will be administered by bolus administrations of 0.1-0.2 mg/kg or a continuous infusion of 20-40 mg per h. **Dosing is based on ideal body weight (men = length in cm – 100; women = length on cm – 105).** During surgery, the target end-tidal PCO2 will be between 4.5 and 5.5 kPa.

During surgery the surgeon will be asked to score the quality of the operating field using the 5-point Leiden Surgical Rating Scale at 10 min intervals. Additionally the following variables will be collected at 10 min interval on the Case Record Form (CRF): blood pressure, heart rate, BIS, intra-abdominal pressure, end-tidal PCO2 and pulmonary pressure. Additionally 30 s video snippets and/or 1 or two photos will be taken during the time of scoring.

At the end of surgery all anesthetic administration will be stopped. In GROUP 1 sugammadex will be administered in a dose of 2 mg/kg, in GROUP 2 in a dose of 4 mg/kg. The time to a TOF ratio > 0.9 will be collected on the CRF as well as all doses of the drugs used including rocuronium, remifentanyl, propofol and sugammadex. After extubation the patient will be transported to the postanesthesia care unit.

In the PACU the following data will be collected: Pain (using an 11 point rating scale), sedation (using an 11 point rating scale), SpO2, blood pressure, heart rate, breathing rate and PQRS. All drugs given to the patient will be collected on the CRF. Additional PQRS will be obtained every 6-hours postoperatively. On the ward pain will be scored twice (8 PM day of surgery and 2 PM next day). We will discriminate between superficial wound pain, deep tissue pain and referred shoulder pain.

The study will be registered at [clinicaltrials.gov](http://clinicaltrials.gov) (or a similar register such as [www.trialregister.nl](http://www.trialregister.nl)).

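### Ward pain is scored at fixed clock times and compared without adjustment for time since surgery, which costs a little precision in that comparison

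*Protocol*

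**What the plan says.** Protocol section 4 (Study procedures) sets the ward schedule: "On the ward pain will be scored twice (8 PM day of surgery and 2 PM next day". Wound, deep tissue and referred shoulder pain are scored separately. Nothing links either score to the start or end of the operation, and the protocol sets no hours for surgery.

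The analysis of these scores is in the analysis amendment within section 5: "Pain scores on the ward (wound pain, deep pain shoulder pain) will be averaged and the group comparison will be by t-test". The sentence names a plain two-group comparison with no covariate. It does not say whether the averaging runs over the three pain types, the two times, or both.

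Pain in the recovery unit is handled differently. Section 3 says "In the recovery room (post-anesthesia care unit) the following measurements are made at 10 min interval", so those scores run from the patient's own recovery, and section 5 assigns them to a linear mixed model. The pain sample size also refers to the recovery room. It takes a group difference of 1.0 point, an SD of 1.5 and a 5% significance level, and concludes: "the study has a power > 0.9 to detect a difference with 100 subjects".

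**The concern.** At 8 PM, a patient operated on early in the day is many hours past surgery and a patient operated on late is only a few hours past it. If pain is still falling, part of the difference between their scores reflects elapsed time alone. The t-test leaves that part in the error term.

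Two things follow. The standard error of the ward comparison is larger than it need be. The 8 PM score also has no single postoperative time attached to it, being an average over a mix of earlier and later pain. The ward scores are the only pain measurements after the recovery unit, so they alone show whether any difference lasts. That makes a cheap gain in precision worth having. Because the protocol itself names the t-test, this is not a matter it leaves open.

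**Working it through.** **1. The plan's own figure.** Difference 1.0, SD 1.5, 50 per group, two-sided alpha 0.05 (sidedness is not stated). Power is 0.910 by the noncentral t and 0.915 by the normal approximation, so the stated power above 0.9 is reproduced. It concerns recovery-room pain. No ward SD or ward difference is given, so SD 1.5 is borrowed below as a yardstick.

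**2. The 8 PM score alone.** Assume surgery ends uniformly over a window of W hours and pain falls by b points per hour that evening. The added SD is b × W/√12, and the relative rise in variance is (added SD/1.5)². The equivalent loss of patients per group is 50 − 50/(1 + rise).

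| W (h) | b (points/h) | Added SD | Rise in variance | Patients lost per group |
|---|---|---|---|---|
| 6 | 0.1 | 0.173 | 1.3% | 0.7 |
| 6 | 0.2 | 0.346 | 5.3% | 2.5 |
| 6 | 0.3 | 0.520 | 12.0% | 5.4 |
| 8 | 0.1 | 0.231 | 2.4% | 1.2 |
| 8 | 0.2 | 0.462 | 9.5% | 4.3 |
| 8 | 0.3 | 0.693 | 21.3% | 8.8 |

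**3. The average of both times.** The 2 PM score is taken later on the curve, where pain changes less with elapsed time, so averaging dilutes the effect. Assume an exponential decline with surgery ending uniformly from 09:00 to 15:00 or to 17:00, and SD 1.5 for the average.

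| Starting pain, half-life | Rise in variance, end by 15:00 | Rise in variance, end by 17:00 |
|---|---|---|
| 5, 6 h | 2.3% | 5.3% |
| 5, 12 h | 2.0% | 4.1% |
| 5, 24 h | 1.1% | 2.1% |
| 3, 12 h | 0.7% | 1.5% |

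The extremes convert to 50 − 50/1.007 = 0.3 and 50 − 50/1.053 = 2.5 patients per group. For the 8 PM score alone, the same curves give 1.6% to 16.6%.

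**4. Check by a simpler route.** If the curve is flat by 2 PM, averaging halves the added SD. The range in step 2 becomes (0.173/2)²/2.25 = 0.3% to (0.693/2)²/2.25 = 5.3%. If each score has SD 1.5 and the two correlate at an assumed 0.5, the average has SD 1.5 × √0.75 = 1.30 and the range is 0.4% to 7.1%. The top figure needs the widest window and the steepest slope together, and equals 50 − 50/1.071 = 3.3 patients.

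**5. One time term is enough.** From 8 PM to 2 PM next day is 18 h for every patient at the scheduled times. Hours to the second score are therefore hours to the first plus a constant. Over the curves in step 3, a straight line in the end time of surgery explains at least 98% of the timing variance in the average. Start of anaesthesia will capture somewhat less, because operations differ in length.

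**6. Cost of the term.** With 100 patients in two groups, a covariate that explains nothing is expected to raise the variance of the group difference by about 1/(100 − 4) = 1.0%. At the bottom of the range, adjustment therefore gains nothing. Over the rest it gains a little.

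**The case against.** The strongest reply is that nothing here is stated wrongly. Clock times are the same in both groups and practical on a ward, and an evening score and a next-afternoon score are easy to interpret. Every timing input above is assumed. The SD of 1.5 may already contain the timing spread, in which case adjustment would improve on the planned precision rather than restore it. All of this stands. It limits the point to a small and conditional one.

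Three stronger readings are tempting, and the protocol does not support them.

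- *That the comparison is biased.* Randomisation balances time of day between groups in expectation. Only precision is affected.
- *That the stated power for pain is wrong.* Power would drop below 0.90 once the SD exceeded about 1.53, so the margin is thin. But that figure belongs to recovery-room pain, which is not scored by the clock. Early pain is also captured there, so an early effect is not lost.
- *That ward pain should move to the times of the recovery-quality scale.* Section 4 says "Additional PQRS will be obtained every 6-hours postoperatively", but it gives no starting point and does not state a 24 h assessment. No analysis linking the two measures is planned. Fixed hours also have a price: a 6 h score after surgery ending at 17:00 falls at 23:00, and the protocol does not show that all patients are still in hospital at 24 h.

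**Conclusion.** The point holds as a minor one about efficiency. Clock-time scoring combined with an unadjusted t-test leaves time since surgery in the error term of the ward pain comparison, provided that operating times vary and pain is falling. Both conditions are plausible, but the protocol states neither.

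If the analysed score averages both times, the variance rises by roughly 1–5%, or about 1 to 3 of 50 patients per group. The figure of roughly 1–21% applies only to the 8 PM score taken alone, as would matter if averaging were over pain types only; the SD of that composite is not given. The recovery-room outcome and its stated power are unaffected.

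**What to change.** Keep the two clock times. Record the start time of anaesthesia and the time of each ward score. In the section 5 amendment, replace the ward pain t-test by a linear model (ANCOVA) of the averaged score on treatment group and hours from start of anaesthesia to the 8 PM score. State in the same sentence whether the average is over pain types, times or both.

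Count from the start of anaesthesia rather than from extubation. Extubation comes after the block and its reversal, so its timing may depend on the group, and adjusting for it could remove or distort part of the treatment effect. A time before the block can act does not carry that risk.

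The cost is one or two recorded times and one degree of freedom. Moving the scores to fixed hours after surgery is optional. It would remove the spread in elapsed time, but at the price of late-night scores and possibly missed ones after discharge.
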